## Abstract

**Background:**

Insomnia is the most prevalent sleep disorder worldwide. Electroacupuncture is effective in improving sleep quality, daytime fatigue status, and anxiety and depression in patients with insomnia, and this study aimed to investigate the metabolic pathways and their possible mechanisms in response to the efficacy of electroacupuncture in the treatment of insomnia.

**Methods:**

A single-center, double-blind, clinical trial was the study’s design. For this study, a total of 99 participants were enrolled, and they will be split into two groups: one for insomnia and the other for health. There are 33 healthy people in the healthy group and 66 insomnia patients in the insomnia group. Acupuncture treatment will be administered to the intervention group three times a week for four weeks, for a total of twelve treatments, and will be followed up for 3 months. A combination of UPLC-Q/TOF-MS and UPLC-QQQ-MS/MS was used to qualitatively and quantitatively examine the serum of 99 participants. The Pittsburgh Sleep Quality Index (PSQI) and serum metabolomics provided the primary findings. The Insomnia Severity Index (ISI), Hyperarousal Scale (HAS), Fatigue Feverity Scale (FSS), Hamilton Depression Scale (HAMD), Hamilton Anxiety Scale (HAMA), Sleep Diary and The Montreal Cognitive Assessment (MoCA) were the secondary outcomes. For the insomnia group, serum will be collected at baseline, at the end of treatment, and the scale will be collected at baseline, after 4 weeks of treatment, and at 3 months of follow-up. For the healthy group, serum will be collected at baseline.

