### Sample size

2.3

PASS 15.0 software was used to determine the sample size based on the nature of the study, with the control group being the healthy group and the treatment group being the insomnia group. Patients with insomnia use the PSQI score as an observed outcome indicator. Based on the pre-test results and literature review, the mean PSQI score for the drug control group is 10.76 ± 3.32 points, and it is anticipated that this score will decrease by 2.63 points for the insomnia group. The effect size (Effect Size) of the two groups is 0.8, α=0.05, Power=0.9, and this means that the sample size for the treatment group is 52 cases, and the sample size for the health group is 26 cases; taking into account variables like fewer visits, an increase in cases, and an increase in cases. The sample size for the treatment group was 52 cases, and the sample size for the healthy group was 26 instances. After taking lost visitation into account, the sample size was expanded by 15%, resulting in 66 cases for the treatment group and 33 cases for the healthy group in this experiment.

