#### Assessment time point

2.8.3

The insomnia group will have the above information completed at enrollment and after 12 treatments, the scale will be collected again at 3 months follow up, and the health group will have serum collected only at the first enrollment.

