### Statistical analysis

2.13

In this study, the software SPSS25.0 was first used to process the experimental data, and the measurement data were expressed by `x ± s, and the count data were expressed by the rate or the constitutive ratio. Comparison of the measurement data between the two groups was firstly analyzed by normality analysis, a t-test was used for the measurement data that conformed to normality and chi-square, and a non-parametric rank-sum test was used for the measurement data that did not conform to the normal distribution; chi-square or Fisher’s exact probability method was used for the count data. p<0.01 was taken as the difference was significant; p<0.05 was taken as the difference was statistically significant between the two groups.

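### Two unranked primary outcomes and two post-baseline PSQI visits share an undivided alpha of 0.05, with no primary PSQI time point and no rule for combining the primaries

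*Protocol article*

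**What the plan says.** The abstract states that "The Pittsburgh Sleep Quality Index (PSQI) and serum metabolomics provided the primary findings". Section 2.8.1 gives each outcome its own subsection under the primary heading and ranks neither. Section 2.8.1.1 describes how PSQI is scored but gives no change measure, comparison or time point.

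On timing, the abstract says that for the insomnia group "the scale will be collected at baseline, after 4 weeks of treatment, and at 3 months of follow-up". Section 2.8.3 repeats that "the scale will be collected again at 3 months follow up", following assessments at enrolment and after the treatment course. Neither post-baseline visit is singled out. In the same section, "the health group will have serum collected only at the first enrollment".

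Section 2.3 bases the sample size on PSQI: "Patients with insomnia use the PSQI score as an observed outcome indicator". It gives no time point and describes the comparison as "the control group being the healthy group and the treatment group being the insomnia group", with an alpha of 0.05 and power of 0.9.

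Section 2.13 lists generic two-group tests (t-test, rank-sum, chi-square or Fisher) and says "p<0.05 was taken as the difference was statistically significant between the two groups", with a further label at p<0.01. It lists no paired or before-after test and no allocation of alpha. Section 2.9.3.2.4 screens metabolites with VIP>1 and p<0.05. The Introduction and Discussion describe two metabolite contrasts: insomnia versus healthy, and before versus after treatment.

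**The concern.** A protocol should fix which result decides the trial, and this one leaves at least three candidates open: PSQI at week 4, PSQI at month 3, and the metabolomics. They can disagree. PSQI may improve at the end of the course and drift back by month 3, or it may change while the metabolites do not. With no primary time point and no combination rule, a favourable result on any of them could later be presented as the primary finding, each judged against the full 0.05.

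The only PSQI contrast in the text does not close the gap, because it compares patients with a group for whom no PSQI is scheduled. The study is meant to supply evidence for electroacupuncture in insomnia, so the reader needs to know beforehand which comparison carries that weight.

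**Working it through.** **1. What the stated sample size spends.** Inputs from section 2.3: difference 2.63, SD 3.32 (ratio 0.79, given as 0.8), alpha 0.05, power 0.90, allocation 2:1.

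Healthy-group n = (1 + 1/2) × (1.960 + 1.282)² × (3.32/2.63)² = 1.5 × 10.51 × 1.594 ≈ 25.1, rounded up to 26, hence 52 patients.

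A t-test calculation with effect size 0.8 gives 25.3, again 26 and 52. A one-sided 0.05 gives 21 and 42, which does not match. The plan's 52/26 therefore reproduces with the whole two-sided 0.05 given to one PSQI comparison. Nothing is reserved for a second visit or a second primary.

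**2. Whether that comparison can be made.**
- Section 2.3 compares insomnia with healthy.
- Section 2.8.3 schedules serum for the healthy group, and no section schedules a PSQI for them, so the contrast has no data on one side.
- Groups A and B of the insomnia arm receive the same acupuncture (section 2.6) and differ only in the metabolomic technique (section 2.1). Comparing them cannot test treatment either.
- What remains is change within patients, for which section 2.13 names no test.

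**3. Family-wise error if either PSQI visit may count.** Assumptions: no true change at either visit, each tested at two-sided 0.05, bivariate normal statistics with correlation r. The documents give no r, so a range is shown. With r = 0 the rate is 1 − 0.95² = 9.75%. For r > 0 it is P(|Z1| > 1.96 or |Z2| > 1.96). Adding metabolomics as one independent test gives 1 − (1 − pair rate) × 0.95.

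| r between PSQI visits | PSQI pair | plus one independent metabolomics test |
|---|---|---|
| 0 | 9.75% | 14.3% |
| 0.3 | 9.5% | 14.0% |
| 0.5 | 9.1% | 13.6% |
| 0.7 | 8.3% | 12.9% |
| 0.9 | 7.0% | 11.7% |

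Counting metabolomics as one test is generous, since section 2.9.3.2.4 tests metabolites individually.

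**4. The opposite rule.** If success required all the primary tests to be significant, a false claim would need every one of them to reject, and the rate could not exceed 0.05. The inflation in step 3 therefore depends on which rule applies, and the document states neither.

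**The case against.** Several points on the other side are fair.

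- A reader might infer that no contrast is named at all. That goes too far. Section 2.3 names a PSQI contrast, and the Discussion sets out the metabolomic contrasts in order: first insomnia versus healthy, then before versus after. But the PSQI contrast cannot be estimated, and the Discussion gives an order of work, not a ranking of outcomes.
- A reader might infer that section 2.13 applies 0.05 to every comparison. It does not say so. It describes two-group comparisons and is silent on before-after tests. The rates in step 3 are therefore for tests that the trial would need but the section does not specify.
- A reader might infer that the plan lets any one favourable result make the trial positive. The text neither states nor excludes this. The 7% to 10% and 12% to 14% are conditional on that rule.
- A reader might extend the count to the seven secondary instruments. Secondary outcomes conventionally carry no trial-wide alpha control, so they do not bear on a point about the primaries.
- The aim is mechanistic, so metabolomics has a legitimate claim to primary status. That stands, and nothing here requires demoting it.
- A detailed testing order may sit in an analysis plan that is not shown. That is true of the order. The primary time point and how two primaries combine are core protocol content, and this article has dedicated sections for outcomes, timing and statistics that leave both open.

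Using PSQI for the sample size hints that it leads, but no sentence says so, and the hint carries no time point.

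**Conclusion.** The point holds in limited form. The protocol leaves the primary PSQI time point and the relation between its two primaries unstated, at an undivided 0.05. Its one named PSQI contrast cannot be estimated from the scheduled data.

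Under an either-wins reading, the family-wise error is about 7% to 10% for the two PSQI visits and about 12% to 14% with one independent metabolomics test added. These sizes rest on assumed correlations (0.9 to 0), on metabolomics counted as a single independent test, and on a decision rule the document does not give. They show what the ambiguity permits, not an error rate the plan has adopted.

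Controlling alpha will not by itself secure an efficacy conclusion. All insomnia patients receive the same treatment and are selected on PSQI above 5 and below 17, so a before-after change cannot separate treatment effect from regression to the mean or natural course. The matter should be settled before analysis. Section 2.14 says recruitment is under way, so a clarification would still be credible.

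**What to change.** In the abstract and sections 2.8.1 and 2.13:

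- Name within-patient change in PSQI total from baseline to week 4, in all insomnia patients, as the primary clinical contrast, with a paired analysis at two-sided 0.05.
- Test month-3 PSQI only if week 4 is significant. This fixed sequence keeps the PSQI error at 5% without splitting alpha.
- If metabolomics stays primary, call it the mechanistic primary. State that it answers a separate question, has its own error control, and cannot by itself support an efficacy claim.
- State that the PSQI contrast is an uncontrolled before-after comparison, with the limits that follow.
- State in section 2.3 that the two-group calculation does not size this contrast. It shares the instrument only: it is a 2:1 comparison using a reference mean from a drug control group that is not in this trial, and no SD of change is given.

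The cost is wording and a registry update, with no added patients or data. The small downside is that month-3 PSQI can no longer make the trial positive on its own.

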**Discussion:**

This study aimed to assess the modulatory effects of electroacupuncture on relevant metabolic markers using serum metabolomics, to explore the potential mechanisms and relevant metabolic pathways of electroacupuncture for the treatment of insomnia, and to provide strong scientific evidence for the treatment of insomnia by electroacupuncture.

**Trial registration:**

ChiCTR2400085660 (China Clinical Trial Registry, http://www.chictr.org.cn, registered on June 14, 2024)

## Introduction

1

The most common sleep disorder in the world, insomnia is defined by clinically frequent and persistent problems getting to sleep, staying asleep, and/or waking up early. It is also characterized by dysfunction during the day, including weariness or low energy, mood swings, and cognitive decline (1). According to reports, 10% of people fit the diagnostic criteria for insomnia, while an additional 15%–20% of adults sporadically experience the symptoms of insomnia, with the percentage of adults experiencing insomnia rising each (2, 3). Patients’ physical and mental well-being are gravely endangered by insomnia, which also places a significant financial strain on the healthcare system (4). Research has demonstrated that sleeplessness raises the risk of a number of chronic physical illnesses, including diabetes, hypertension, heart disease, cancers, and mental health issues (5–8). The neurobiological mechanisms of insomnia are unknown, and most scholars believe that insomnia occurs as a result of psychological and physiological hyperarousal of the organism. Current diagnostic methods for insomnia rely on subjective patient reports, sleep diaries, and clinical interviews, and lack quick and accurate objective markers, such that insomnia is underdiagnosed in primary care settings thus leading to exacerbation of the condition (9–11). In addition, insomniacs undergoing treatment may lack objective knowledge and suffer from deep cognitive rumination, thus compromising clinical outcomes. Modern medical treatment of insomnia includes medication and cognitive behavioral therapy. However, commonly used sedative and sleeping medications in clinical practice are often accompanied by different degrees of adverse effects, including dizziness, headache, daytime sleepiness, and increased risk of dementia, leading to low patient acceptance (12). Cognitive-behavioral therapy is a first-line therapy recommended by clinical guidelines, which is more difficult to implement clinically due to its lack of professional resources, time-consuming nature, and poor patient compliance (13). Electroacupuncture is effective in treating insomnia with a non-placebo effect (14), but the specific mechanism of its effect is unknown, and its efficacy assessment is mainly based on the patient’s subjective scale, which lacks objective assessment indexes and testing methods.

In order to investigate the pathophysiology of diseases and the mechanisms by which therapies work, metabolic technologies is used to identify the various changes that occur in biological systems under various medical conditions. It also facilitates the rapid and thorough analysis of differential metabolites to elucidate physiological or pathological pathways of metabolism (15). Additionally, the technology explores the relationship between pathophysiological changes and small molecule metabolites. 328 metabolites are thought to be very important in human sleep, and particularly abundant metabolites include carnitine, aromatic amino acids, phosphatidylcholine, and lysophosphatidylcholine (16).Previous studies have explored the unique serum metabolomic profile of insomnia and found that insomnia induces perturbations in metabolites of amino acid metabolism, neurotransmitter metabolism, and glycolipid metabolic pathways (17). One study showed that by collecting plasma from insomnia patients and applying untargeted metabolomics analysis, 64 metabolites were associated with sleep duration, and elevated levels of amino acid metabolites (such as branched-chain amino acids and gamma-glutamyl dipeptide) were associated with later sleep duration (18). In another study, elevated energy metabolites and reduced branched-chain amino acid catabolic metabolites, as well as altered glucose metabolism, were observed in patients with insomnia by comparing insomnia patients with healthy controls, suggesting an increased susceptibility to diabetes in insomnia patients (19). Insomnia leads to significant alterations in specific metabolic pathways, which may be evidence of a link between insomnia and other somatic and psychiatric disorders. Therefore, this study aims to utilize metabolomics techniques to qualitatively and quantitatively analyze the sera of healthy individuals and patients with insomnia, in order to screen for differential metabolites, further explore the possible pathogenesis of insomnia, and search for objective biomarkers for it.

In addition, the development and translational application of metabolomics technology can not only be used to explore the pathogenesis of insomnia but also provide a new platform for constructing therapeutic strategies for insomnia. Studies have found that insomnia patients who take benzodiazepine receptor agonists and benzodiazepines have poor glucose metabolism (20), while exogenous melatonin significantly reduces glucose tolerance and increases insulin resistance in subjects (21). This suggests that medication may have adverse metabolic effects. A preliminary study of electroacupuncture Shenmen-Sanyinjiao acupoint pairing using non-targeted metabolomics techniques found that the Shenmen-Sanyinjiao pairing significantly potentiated serum glycerophosphatidylserine-like metabolites in patients with insomnia, resulting in a significant improvement in the impairment of diurnal functioning in insomnia patients (22). However, the current study lacked quantitative analysis of specific metabolites to observe the dynamic change pattern under electroacupuncture intervention. Therefore, it is necessary to conduct more in-depth studies to provide a scientific basis for the mechanism of action of electroacupuncture.

Ultra-high performance liquid chromatography (UPLC) coupled with mass spectrometry offers the benefits of high resolution, high sensitivity, and high efficiency with the advancement of analytical instruments, enabling quick qualitative and quantitative examination of samples. Furthermore, blood is a frequently utilized specimen in metabolomics technology because it is simple to obtain, has the ability to represent metabolite changes under a variety of intervention and pathophysiological settings, and is a valuable source of disease biomarkers. Based on this, we set up a clinical trial, using ultra high performance liquid chromatogravimetric quadrupole time-of-flight mass spectrometry (UPLC-Q/TOF-MS) and ultra-high performance liquid chromatogravimetric triple quadrupole tandem mass spectrometry (UPLC-QQQ-MS/MS) for qualitative and quantitative analysis of subjects’ serum. To screen out the metabolite differences between healthy people and insomniacs and insomniacs before and after treatment, explore the correlation between pathophysiological changes in insomnia and small molecule metabolites, as well as the metabolic pathway in response to the therapeutic effect of electroacupuncture, and provide scientific evidence for the possible mechanism of electroacupuncture regulating metabolic network in the body to improve insomnia symptoms.

## Materials and methods

2

### Study design

2.1

The study design is a single-center, double-blind, clinical trial to investigate the metabolic pathways and possible mechanisms underlying the efficacy response of electroacupuncture for insomnia. The study protocol follows the SPIRIT guidelines, 99 subjects will be recruited and divided into an insomnia group and a healthy group. The International Classification of Sleep Disorders, Third Edition (ICSD-3) diagnostic criteria will be used to diagnose subjects with insomnia. Those who meet the inclusion criteria will also sign an informed consent form, complete the following scale assessments, and have their serum collected: PSQI and ISI to measure sleep; HAS to measure hyperarousal state; HAMD and HAMA to measure mental state; and FSS to measure physical and mental fatigue, sleep diary to measure sleep behavior, and MoCA to measure cognition to gather baseline assessment data. This will be followed by 4 weeks of treatment. Retesting of the above scales will be completed at the end of treatment and at 3 months follow-up, as well as serum collection’s will be completed at the end of treatment. The healthy group will complete serum collection at enrollment. The insomnia group will be randomly divided into Group A and Group B, matched with the healthy group. Group A and the healthy group will be screened for differential metabolites using metabolomics analysis with non-targeted UPLC-Q/TOF-MS, and Group B will be quantified for the screened differential metabolites using metabolomics with targeted UPLC-QQQ-MS/MS. The flow chart of the experiment is shown in **Figure 1**. The flow schedule is shown in **Figure 2**.

**Figure 1 f1:**
[figure not shown]
Flow diagram of the trial.

**Figure 2 f2:**
[figure not shown]
Schedule of enrolment, interventions, and assessments.

### Participants

2.2

#### Patient recruitment

2.2.1

Patients with insomnia will be recruited in this study in the following three ways: 1) cases will be recruited from the Acupuncture and Rehabilitation Department and Physical Examination Center of Jiangsu Provincial Hospital of Traditional Chinese Medicine (JSTH); 2) recruitment posters will be placed in the outpatient department of Jiangsu Provincial Hospital of Traditional Chinese Medicine (JSTH); 3) WeChat platform will be used to push out the recruitment articles.

#### Inclusion criteria

2.2.2

##### Inclusion criteria for insomnia patients

2.2.2.1

Age 18-60 years old;Meet ICSD-3 diagnostic criteria;5 points < PSQI < 17 points;not receiving psychotropic medication;have no communication or cognitive impairment and can perform basic operations on a smartphone;Signed informed consent.

##### Inclusion criteria for healthy people

2.2.2.2

Normal blood count, liver function, kidney function, electrocardiogram, blood glucose, and blood lipid after consultation and health examination; healthy, no previous organic or functional diseases or psychiatric disorders;Be in the age range of 18 to 60;not recently participated in other clinical studies;Voluntarily participate in this trial, agree to and sign the informed consent form.

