##### Exclusion criteria for insomnia patients

2.2.3.1

Neuroendocrine, cardiovascular, cerebrovascular, hematopoietic system, tumor and other serious diseases;Sleep disorders caused by depression, anxiety, schizophrenia or other serious mental illnesses with HAMA score >14 and/or HAMD score >17;Other sleep disorder disorders such as obstructive sleep apnea, rapid eye movement (REM) sleep disorder or restless legs syndrome;Those who are not suitable to receive acupuncture treatment, such as those who are pregnant or breastfeeding;Those who have received acupuncture treatment for insomnia in the past month;those with alcohol and/or other drug abuse or dependence.

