##### Exclusion criteria for healthy people

2.2.3.2

Pregnant and lactating women;Alcoholics and smokers.

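### Controls are screened on laboratory tests, disease history and smoking but patients are not, so metabolites tied to those filters are expected to differ between Group A and controls even if insomnia has no effect

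*Protocol article*

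**What the plan says.** **Controls.** Section 2.2.2.2 requires "Normal blood count, liver function, kidney function, electrocardiogram, blood glucose, and blood lipid after consultation and health examination" and adds "healthy, no previous organic or functional diseases or psychiatric disorders". Section 2.2.3.2 also excludes "Alcoholics and smokers".

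**Patients.** The inclusion list in 2.2.2.1 begins "Age 18-60 years old;Meet ICSD-3 diagnostic criteria;5 points < PSQI < 17 points;not receiving psychotropic medication"; the remaining items concern communication and cognition, smartphone use and consent. The medical exclusion in 2.2.3.1 is "Neuroendocrine, cardiovascular, cerebrovascular, hematopoietic system, tumor and other serious diseases". Neither list contains a laboratory test, a laboratory threshold or a smoking rule. Alcohol, pregnancy and psychiatric illness do have counterparts in both groups.

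**Use of the comparison.** The abstract states: "The Pittsburgh Sleep Quality Index (PSQI) and serum metabolomics provided the primary findings". Section 2.1 states: "Group A and the healthy group will be screened for differential metabolites using metabolomics analysis with non-targeted UPLC-Q/TOF-MS". Section 2.9.3.2.4 selects metabolites by VIP>1 together with a two-sided test at p<0.05 and names no covariate. Section 2.1 says that the patient groups are matched with the healthy group but names no matching factor.

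**Expected biology.** The Introduction reports that "insomnia induces perturbations in metabolites of amino acid metabolism, neurotransmitter metabolism, and glycolipid metabolic pathways".

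**The concern.** Someone with raised glucose or lipids and no serious disease can enter as an insomnia patient. The same person without insomnia could not be a control. The control group is therefore cut off at the limits of several serum tests and the patient group is not. The groups are then compared on serum metabolites, including pathways that the Introduction links to insomnia and that overlap with those tests. The controls-only smoking exclusion is a filter of the same kind.

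A shift produced this way is a real difference between the two groups as recruited, but eligibility causes it, not insomnia. Matching on age and sex would not remove it, nor would a multiplicity correction. Targeted quantification in Group B would not remove it either, because those patients enter under the same rules: it can confirm the measurement but not the attribution.

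The Group A versus healthy list feeds the pathway analysis, the choice of Group B targets and, according to the Discussion, the check of whether abnormal levels return towards normal after treatment. Metabolites that enter the list through eligibility would be carried into all three as features of insomnia.

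**Working it through.** **The plan's own figure.** The document gives no figure for this effect. Its sample size rests on PSQI and does not bear on it.

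**Inputs.**
- Group sizes of 33 versus 33. Section 2.3 gives 66 patients and 33 controls, and a 1:1 split gives 66/2 = 33 in Group A. Section 2.5 speaks of 33 patients being split into A and B, so 33 in Group A is an assumption.
- Test level 0.05, two-sided (section 2.9.3.2.4).
- Assumed: the share p of otherwise eligible people who would fail a one-sided upper limit, from 5% to 40%.
- Assumed: the correlation r of a metabolite with the screened analyte.
- Assumed: the fraction f of abnormal patients whom the disease exclusion in 2.2.3.1 removes, 0 or one half.

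**Expected shift with no insomnia effect.** Take the analyte as standard normal, with z its (1 − p) quantile and φ the normal density.
- Control mean: −φ(z)/(1 − p).
- Patient mean: −fφ(z)/(1 − fp), which is 0 when f = 0.
- Difference (patients minus controls) for the analyte: φ(z)/(1 − p) − fφ(z)/(1 − fp). A metabolite with correlation r shifts by r times this.

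Example with p = 0.20: z = 0.842 and φ(z) = 0.280. With f = 0 the shift is 0.280/0.80 = 0.35 SD. With f = 0.5 it is 0.35 − 0.140/0.90 = 0.19 SD.

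| p | 5% | 10% | 20% | 30% | 40% |
|---|---|---|---|---|---|
| Shift in SD, r = 1, f = 0 | 0.11 | 0.20 | 0.35 | 0.50 | 0.64 |
| Shift in SD, r = 1, f = 0.5 | 0.06 | 0.10 | 0.19 | 0.29 | 0.40 |

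**Chance of p<0.05 with no insomnia effect.** Two-sample t-test, 33 versus 33, 20,000 simulated trials per cell:

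| p | 5% | 10% | 20% | 30% | 40% |
|---|---|---|---|---|---|
| f = 0, r = 1 | 6.9% | 13.1% | 34.9% | 63.6% | 86.6% |
| f = 0, r = 0.7 | 6.2% | 8.6% | 17.5% | 32.0% | 49.4% |
| f = 0, r = 0.5 | 5.1% | 7.0% | 11.0% | 17.8% | 26.1% |
| f = 0, r = 0 | 5.0% | 5.0% | 4.9% | 5.0% | 4.8% |
| f = 0.5, r = 1 | 5.4% | 7.1% | 14.8% | 29.6% | 51.5% |
| f = 0.5, r = 0.7 | 5.4% | 6.0% | 9.0% | 14.4% | 23.0% |
| f = 0.5, r = 0.5 | 5.1% | 5.5% | 6.6% | 9.7% | 13.0% |

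The expected shift is non-zero whenever some eligible patients would fail the control rule and r is not 0. It vanishes for unrelated metabolites (r = 0) or if both groups face the same rule. The rates are upper bounds on entry to the list under these assumptions, because VIP>1 is required as well. A normal range with symmetric limits on both sides would not move the mean, so the one-sided limit is also an assumption and will not suit every listed test.

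**The case against.** Screened healthy controls are a common choice in an exploratory metabolomic screen, and the limitations section calls for more influencing factors to be considered and for further validation. The article is condensed, so the full protocol may describe a patient work-up that it omits. The patients' disease exclusion, and the history and physical examination before treatment in section 2.10, remove some abnormal patients. At failure rates of 5% to 10% the excess over 5% is small. The outcome definition in 2.8.1.2 concerns biomarkers of electroacupuncture treatment, and the before/after contrast lies within patients.

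Much of this stands as a limit on size and reach. It does not remove the asymmetry. Both eligibility lists are given, they differ, and section 2.10 looks for contraindications to electroacupuncture without setting a laboratory limit. The limitations section names short follow-up, the single centre and non-fasting serum, but not unequal selection.

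A reader might infer more: that controls are selected on the primary outcome as such, that a significant metabolite difference is bound to appear, or that the treatment comparison is biased. The documents do not support these readings. PSQI, the other primary outcome, is untouched. The filter acts on clinical chemistry that only partly overlaps the serum profile. Significance depends on p and r, which are not given. An eligibility offset between groups does not itself produce a change within patients; it affects only which metabolites are followed.

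**Conclusion.** The point holds for one contrast and one class of metabolites: Group A versus the healthy group, for metabolites related to the screened tests. There a difference is expected without any effect of insomnia, and nothing in the stated matching or analysis corrects it. Its size cannot be fixed from the document. For a screened analyte itself the false-positive rate is about 7% to 87% over assumed failure rates of 5% to 40% with patients wholly unscreened, and about 5% to 52% if half of the abnormal patients are excluded. Both ranges rest on the assumptions listed in the working. The effect of the smoking rule was not quantified.

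This should be fixed, because the screen determines what is carried forward and read as the pathogenesis of insomnia. With the failure rate and correlations unknown, it does not invalidate the trial.

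**What to change.** Recruitment is open (section 2.14), so an amendment can still help.

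- **Controls still to be enrolled.** Replace the control-only health, laboratory and smoking filters in 2.2.2.2 and 2.2.3.2 with the disease exclusions that 2.2.3.1 applies to patients. Deleting only the glucose and lipid items would leave the liver, kidney, blood-count, ECG, disease-history and smoking asymmetries. State expressly that controls must not have insomnia, since the present text covers this only through the general health rule.
- **Why not screen the patients instead.** That would also equalise the groups, but the protocol regards glucose and lipid changes as possible consequences of insomnia, so it could remove true effects.
- **Controls already enrolled.** State that differences in glucose-, lipid-, liver- and kidney-related metabolites cannot be attributed to insomnia from this contrast alone. Where patient laboratory and smoking data exist, add a sensitivity analysis restricted to Group A patients who would have met the control criteria. The article plans no such patient data, so this subgroup may not be identifiable.

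Cost: a short eligibility amendment, slightly more heterogeneous controls, some controls recruited under each rule, and a narrower claim.
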